## 7.2 Preliminary Efficacy Exploratory Measures

1) Functional measures:

A. BCVA: Early Treatment Diabetic Retinopathy Study Visual Acuity Scale (ETDRS Chart) is used to examine and compare the changes in visual acuity at each time point at pre-dose (baseline period), D1, D2, D3, D14, D28, D60, D90, D180, D270 and D365 post-dose, and 15 months after the end of observation period;

B. Color vision test: Atlas for colorblindness is used to compare the changes in color vision at each time point at pre-dose (baseline period), D28, D60, D180 and D365 post-dose, and 15 months after the end of observation period;

C. Dark-adapted contrast sensitivity test: This test is used to compare the changes in scotopic contrast sensitivity at each time point at pre-dose (baseline period), D28, D60, D180 and D365 post-dose, and 15 months after the end of observation period;

D. Macular microperimetry and mfERG examination: This examination is used to compare the changes in macular retinal function and macular microperimetry at each time point at pre-dose (baseline period), D28, D60, D180 and D365 post-dose, and 15 months after the end of observation period;

2) Behavioral measures:

MLMT test is used to compare the behavioral changes of subjects at each time point at pre-dose (baseline period), D28, D60, D180 and D365 post-dose, and 15 months after the end of observation period;

3) Morphological measures:

Color fundus photography, FAF and OCT results are used to examine and compare the changes in retinal morphology and changes in retinal cells in each layer at each time point at pre-dose (baseline period), D1, D2, D3, D14, D28, D60, D90, D180, D270 and D365 post-dose, and 15 months after the end of observation period;

# 8. Adverse Events and Serious Adverse Events

## 8.1 Adverse Events

Definition: An adverse event refers to any undesirable experience occurred by a patient during the study, whether or not related to the study. Adverse events include all unforeseen signs, symptoms, or aggravation of accompanying symptoms or complications.

**Adverse events assessments**

**Severity:** Adverse events are divided into mild, moderate and severe

1) Mild: Symptomatic but not interfering with usual activities;

2) Moderate: Symptomatic and having a slight impact on activities of daily life;

3) Severe: Serious impact on activities of daily life.

**Relationship to the observed drug:** The relationships between adverse events and the observed drug are as follows:

1) Definitely not related: The adverse event is related to other factors such as primary disease, complication, concomitant medication or treatment without temporal relationship to the observed drug.

2) Unlikely related: There is no clear temporal relationship to the observed drug, or it may be related to other factors such as primary disease, complications, concomitant medication or treatment, and the possibility that the observed drug caused it cannot be completely ruled out.

3) Possibly related: There is clear temporal relationship to the observed drug. It is highly suspected that the adverse event is related to the observed drug, and other factors such as primary disease, complications, concomitant medication or treatment cannot be ruled out.

4) Probably related: There is clear temporal relationship to the observed drug. Other factors such as primary disease, complications, concomitant medication or treatment can almost be ruled out.

5) Definitely related: There is clear temporal relationship to the observed drug. Others, such as primary disease, complications, concomitant medication or treatment, may be completely ruled out. The adverse event reappeared after re-administration.

The above items 3-5 should be considered as drug-related adverse reactions and handled as adverse drug reactions. When belonging to items 1-2, it should be detailed in the case report form.

**Method of recording adverse events:**

The investigator should record any undesirable symptoms, diseases or signs experienced by the subject during treatment with the observed drug in the adverse event item of the case report form. The following items need to be recorded:

1) Name and symptoms;

2) Severity;

3) Time of appearance and disappearance;

4) Impact on investigational drug dose:

a: Dose unchanged b: Dose increased c: Dose decreased d: Dose interrupted e: Drug withdrawn.

5) Action taken for the adverse event:

a: No; b: Yes (record concomitant medications and treatments if yes)

6) Outcome after the end of the study:

a: Disappeared; b: Improved; c: Unchanged; d: Unknown.

7) Causal relationship to the observed drug.

Any adverse event that does not disappear after the end of treatment should be followed up until stabilization and safety ensured.

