# 3. Study Design

## 3.1 Overall Design

This is a single-center, open-label, single-arm and single-dose study and aimed to evaluate the safety and preliminary efficacy of the investigational drug in patient with BCD.

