# 7. Study Evaluation

## 7.1. Safety Evaluation

Safety evaluation includes adverse events, vital signs, physical examination, ophthalmological examination, laboratory examination, ECG and immunogenicity.

1) Adverse events: Ocular hypertension (excluding slightly high intraocular pressure within 24 hours postoperative), endophthalmitis, vitreous hemorrhage, subretinal hemorrhage, retinal detachment (excluding within 14 hours postoperative), macular hole;

2) Ophthalmological examination: Visual acuity test, intraocular pressure test (intraocular pressure in both eyes), slit-lamp examination, ophthalmoscopy, color fundus photography and OCT;

3) Vital signs, physical examination, chest X-ray and ECG;

4) General laboratory tests: Blood routine and urine routine, liver function and renal function tests, serum virology tests, coagulation function test.

5) Drug-time curves and mean drug-time curves are plotted for each subject based on rAAV vector DNA concentrations measured in lacrimal fluid and peripheral blood leukocytes at each time point.

6) Immune-time curves are plotted for each subject based on cellular and humoral immune data measured for the therapeutic vector in the blood of subjects in the study.

In addition to observation of systemic adverse events/reactions, the focus is on ocular adverse events/reactions. Criteria for grading ocular adverse events are shown in Appendix 1. Definition of serious (sight-threatening) ocular adverse events is detailed in Appendix 2. Ocular adverse events should be assessed as injection-related complications or drug-related.

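### Section 8.1's adverse-event codes do not fit a single-injection surgical study: no worsened or fatal outcome, a causality level that cannot be reached, and no place to record procedure attribution

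*Protocol*

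**What the plan says.** Section 3.1 states the design: "This is a single-center, open-label, single-arm and single-dose study". The Synopsis (Study Procedure) places the vitrectomy and the subretinal injection on the same day, with oral prednisone before and after.

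Section 8.1 then sets the adverse-event rules.

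- **Outcome at the end of the study:** "a: Disappeared; b: Improved; c: Unchanged; d: Unknown".
- **Effect on dose:** "a: Dose unchanged b: Dose increased c: Dose decreased d: Dose interrupted e: Drug withdrawn".
- **Causality:** one five-level scale, for the observed drug only. Level 2 (Unlikely related) admits an event with no clear temporal link, "or it may be related to other factors such as primary disease, complications, concomitant medication or treatment". Level 5 (Definitely related) includes "The adverse event reappeared after re-administration".
- **Adverse reactions:** "The above items 3-5 should be considered as drug-related adverse reactions and handled as adverse drug reactions".
- **What is to be recorded:** events "experienced by the subject during treatment with the observed drug".

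Section 7.1 adds a separate instruction: "Ocular adverse events should be assessed as injection-related complications or drug-related". Section 8.2 makes death and permanent impairment criteria for a serious adverse event.

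**The concern.** The primary objective is the safety of one subretinal injection, an intervention made up of vector and surgery together. The recording rules read as though written for a drug given repeatedly and without surgery. Three consequences follow.

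- The outcome field cannot say that an event got worse or ended in death, and it does not separate lasting damage from an event that is merely unresolved.
- One causality level and most of the dose-action codes can never apply.
- The attribution that section 7.1 asks for has no field in the section 8.1 record and plays no part in deciding what counts as a reaction.

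At stake is whether the related-event count describes the whole intervention or the vector alone. Attributions not captured on the form cannot be recovered later at the analysis stage.

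**Working it through.** **Inputs.** Single dose (section 3.1). Vitrectomy and injection on the same day (Synopsis). 3 pilot subjects plus 9 new ones = 12 (section 9.1.2), a sum that reproduces. Section 9.1.1 states no hypothesis, so there is no power or alpha calculation to reproduce. The check is mainly a comparison of texts.

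**1. Outcome codes against possible end states.**

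| State at end of study | Code available in 8.1 |
|---|---|
| Resolved | Disappeared |
| Better, still present | Improved |
| Ongoing, no change | Unchanged |
| Settled, permanent deficit | Unchanged, so not distinguishable from the row above |
| Worse | none |
| Death | none |

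The list runs from a to d with no open category. Section 8.2 flags death and permanent impairment as serious, but that is a seriousness criterion and does not fill the outcome field. A non-serious event that worsens has no code at all.

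**2. Repeat-dose wording.** One injection means no re-administration, so Definitely related, read as written, cannot be assigned. Of the five dose-action codes, only the one for an unchanged dose could describe anything after a single injection. Neither fault alters the number of reactions, because levels 3 and 4 also count.

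**3. Causality: section 7.1 beside section 8.1.** Take a retinal detachment a few days after surgery that the investigator thinks may be surgical.

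- Under 7.1 it is an injection-related complication.
- Under 8.1 the second limb of level 2 fits, because complications or other treatment may explain it. It is then not a reaction.
- Level 3 (Possibly related) also fits if there is a clear temporal link and strong suspicion, since it too allows that other causes are not excluded. It is then a reaction.
- Levels 4 and 5 need other causes to be almost or completely excluded, which is hard so soon after a vitrectomy.

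The same event can therefore be in or out of the reaction count according to how the rater weighs suspicion of the drug. The seven items of the 8.1 record include causality to the drug and nothing for the procedure. No rule says that an injection-related complication counts as a reaction.

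**4. Where the event still appears.** Section 9.3.3 summarises the incidence of overall and various adverse events without restricting by causality, so the event is counted there. The narrower count matters because section 3.1 (Safety Study) summarises the 3 pilot subjects as having no serious adverse reaction related to either drug or treatment, which is broader than the drug-only rule in 8.1.

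**5. Scale, as illustration only.** The intervals are exact (Clopper-Pearson). For x = 0 the upper limit is 1 − 0.025^(1/n); for n = 12 this is 1 − 0.7354 = 26.5%. For x = 1 the lower limit is 1 − 0.975^(1/n); for n = 12 this is 0.2%. The other limits come from beta quantiles.

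| Subjects with a reaction | Rate | 95% CI |
|---|---|---|
| 0/12 | 0% | 0% to 26.5% |
| 1/12 | 8.3% | 0.2% to 38.5% |
| 2/12 | 16.7% | 2.1% to 48.4% |
| 0/9 | 0% | 0% to 33.6% |
| 1/9 | 11.1% | 0.3% to 48.2% |

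Reclassifying one subject is the difference between some reactions and none.

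**The case against.** The strongest reply is that nothing is lost from the specified safety analysis. Section 9.3.3 and the Synopsis count all adverse events whatever their causality, and neither names a table of adverse reactions. Section 7.1 lists endophthalmitis, haemorrhage, retinal detachment and macular hole as safety events and asks for injection-versus-drug attribution. A perioperative event can be rated Possibly related. Levels 1 and 2 must still be detailed in the case report form. All of this stands, and it limits the point to the related-event count and the quality of the coded record.

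Some stronger readings are tempting, but the documents do not support them.

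- **Surgical complications vanish from the safety results.** They remain in all-event incidence.
- **Deaths and permanent loss of vision go unrecorded.** Section 8.2 captures them as serious events and visual acuity is measured to the last visit. Only the outcome code is deficient. Appendices 1 and 2, on ocular grading and sight-threatening events, are not shown and may add detail.
- **Recording stops on the day of injection.** The 8.1 recording rule does speak of treatment, but the definition in the same section covers the whole study, and Table 1 collects events from V2 to V15. This is loose wording.
- **Section 7.1 omits the reaction the protocol expects, intraocular inflammation.** The dose rationale reports it in the high-dose groups of another product, and section 5.2.3 discusses it under overdose. Neither calls it expected at the trial dose, and the general definition would capture it.
- **Pilot events must be recoded.** The pilot's coding rules are not shown.
- **The repeat-dose wording causes the surgical gap.** It does not. The gap comes from a causality scale that rates the drug alone.

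**Conclusion.** The point holds as a fault in the stated coding rules and should be corrected. Followed exactly, section 8.1 cannot code a worsened or fatal outcome, cannot separate sequelae from an ongoing event, contains a causality level no subject can reach, and gives no place to the attribution that section 7.1 requires. A complication of the vitrectomy or injection can be left out of the adverse-reaction count while remaining in all-event incidence.

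The size cannot be estimated from the documents. The 1/12 against 0/12 contrast shows how sensitive a count of this size is. It is neither a forecast nor a statement about a table the protocol names. The conclusion rests on two readings: that complications and treatment in level 2 can include the surgery, and that treatment in the pilot summary is broader than the drug alone.

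**What to change.** - Add worsened, resolved with sequelae and fatal to the outcome codes in section 8.1.
- Delete the re-administration condition from Definitely related, and mark the dose-change codes not applicable.
- Record causality separately for vector, surgical or injection procedure, and prednisone, allowing more than one or none. This gives the section 7.1 attribution a field.
- Report events related to any study intervention alongside all-event incidence.
- As a wording correction only, align the recording rule in 8.1 with the definition in the same section and with Table 1.

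The cost is protocol and eCRF wording and slightly more data capture per event. The related-event rate may look less favourable than one based on the drug alone.

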## 8.2 Serious Adverse Event

Definition: Fatal; probably life-threatening; requires hospitalization or prolonged hospitalization; results in serious illness or permanent impairment; results in congenital anomaly.

# 9. Statistical Considerations

## 9.1 Statistical Hypothesis and Sample Size Estimation

### 9.1.1 Statistical hypothesis

This study is an exploratory study on the trend of safety and efficacy, without statistical hypothesis.

### 9.1.2 Sample size estimation

It is estimated to add 9 subjects based on 3 subjects in the preliminary study, 12 subjects in total, with 1 dose group.

## 9.2. Analysis Populations

The statistical analysis data sets for this study are defined as follows.

Full Analysis Set (FAS): According to the intention-to-treat (ITT) principle, all subjects who sign informed consent form and are eligible for screening will be included in the full analysis set of this study, except for major GCP violations.

Safety Set (SS): Including subjects in FAS who use the investigational drug and have safety assessment.

Per-Protocol Set: Including subjects in the FAS who have no major protocol deviations that may significantly affect the primary efficacy endpoint of the study, so subjects with major protocol deviations must be excluded from this analysis population (dose adjustment or discontinuation due to toxicity is not a protocol deviation). The definition of major protocol deviations is discussed and determined prior to the data review meeting. At this meeting, compliance and other protocol violations are used to identify major protocol violations.

All analysis sets will be decided at a data review meeting.

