# 2. Study Objectives

**Primary Objective:** To evaluate the safety of a single subretinal injection of rAAV2/8-hCYP4V2 in patients with Bietti's crystalline dystrophy (BCD).

**Secondary Objective:** To preliminarily explore the clinical efficacy of rAAV2/8-hCYP4V2 gene replacement therapy.

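### As written, a treated subject removed from the Full Analysis Set also leaves the Safety Set, the only population defined for the primary safety objective

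*Protocol*

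**What the plan says.** The primary objective in Protocol section 2 is "To evaluate the safety of a single subretinal injection of rAAV2/8-hCYP4V2 in patients with Bietti's crystalline dystrophy (BCD"). Efficacy is secondary and exploratory. Section 3.1 describes the design: "This is a single-center, open-label, single-arm and single-dose study".

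Section 9.2 builds its analysis sets from the FAS:

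- **FAS.** It invokes the intention-to-treat principle and says that "all subjects who sign informed consent form and are eligible for screening will be included in the full analysis set", but then adds "except for major GCP violations". The protocol does not say what counts as such a violation.
- **Safety Set.** "Including subjects in FAS who use the investigational drug and have safety assessment".
- **Per-Protocol Set.** FAS subjects "who have no major protocol deviations that may significantly affect the primary efficacy endpoint of the study". Major protocol deviations are to be defined before the data review meeting.
- **Timing.** "All analysis sets will be decided at a data review meeting". No date is given.

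Section 9.3.3 describes adverse event incidence and the other safety summaries without naming an analysis set. Section 9.3.4 assigns all efficacy data to both the FAS and the Per-Protocol Set.

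**The concern.** A safety population should follow exposure. A GCP breach, such as a consent or documentation failure, does not undo a subretinal vector injection, and whatever then happens to that subject is part of the safety experience with the product. Because the Safety Set is a subset of the FAS, a rule written for the FAS also decides who is counted for safety.

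Two features add to this. The term that controls FAS membership, and hence Safety Set membership, is undefined. The decision is also left to a meeting in a study where nobody is blinded. At stake is the denominator, and possibly the numerator, of the adverse event incidences that answer the primary objective. With at most 12 subjects, one person is a visible share of the result.

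**Working it through.** **Inputs**

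- Set definitions and the data review meeting: section 9.2.
- Primary objective: section 2. Open-label, single-arm design: section 3.1.
- Safety analysis: section 9.3.3.
- Sample size: section 9.1.2. Confidence level of 95%: section 9.3.1. The interval method is not stated there, so I use the exact (Clopper-Pearson) interval.
- Number of affected subjects: not in the protocol; assumed to be 1, then 2.

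**Step 1: the nesting.** Written as conditions:

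- FAS = consent signed AND eligible for screening AND no major GCP violation.
- Safety Set = in FAS AND drug used AND safety assessment available.

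Substituting the first into the second, a subject who was dosed and assessed but has a major GCP violation fails the FAS condition and so fails the Safety Set condition. This needs only the GCP clause. The last condition can also drop a dosed subject who has no recorded safety assessment.

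**Step 2: is there a safeguard elsewhere?** Section 9.3.3 names no set, so the Safety Set applies by its name and because no other safety population is defined. Sections 7.1 and 8.1 cover collection and recording of safety data, not the population for the incidence tables. No sentence retains a dosed subject who has been removed from the FAS.

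**Step 3: control over membership.** Section 9.2 requires prior definition only for the deviations that govern the Per-Protocol Set. The GCP clause has no such rule. The meeting's timing is not stated, but the study is open-label. Section 5.1.2 also makes each new subject's start conditional on 14 days without significant toxicity in the one before, so early safety outcomes are looked at as the study runs. That outcomes are known by the meeting is therefore a reasonable inference.

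**Step 4: possible size.** The protocol's own figure reproduces: 3 + 9 = 12. There is no power or precision calculation to check.

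For x affected of n, the exact 95% limits are: lower = 2.5% quantile of Beta(x, n − x + 1); upper = 97.5% quantile of Beta(x + 1, n − x). For x = 0, the lower limit is 0 and the upper is 1 − 0.025^(1/n). For example, with n = 11: 1 − 0.025^(1/11) = 0.285.

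| Assumed case | All dosed subjects counted | One affected subject dropped |
|---|---|---|
| 12 subjects, 1 affected | 1/12 = 8.3% (0.2% to 38.5%) | 0/11 = 0% (upper limit 28.5%) |
| 12 subjects, 2 affected | 2/12 = 16.7% (2.1% to 48.4%) | 1/11 = 9.1% (0.2% to 41.3%) |
| 9 new subjects, 1 affected | 1/9 = 11.1% (0.3% to 48.2%) | 0/8 = 0% (upper limit 36.9%) |

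**Step 5: the Per-Protocol Set wording.** Section 2 makes efficacy secondary, section 9.1.1 states that there is no hypothesis, and section 7.2 lists measures without calling any of them primary. The exclusion rule for the Per-Protocol Set therefore points to an endpoint the protocol does not name.

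**The case against.** The strongest reply is that the text is milder than it can be made to sound. Several parts of that reply stand.

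- **Eligibility.** A reader might infer that anyone dosed and later found ineligible is dropped. The FAS wording ties entry to screening under an intention-to-treat principle and is ambiguous. It may mean found eligible at screening, but it does not clearly remove someone who passed screening and was dosed. Neutralizing antibody testing is scheduled at screening, and genetic results are checked when eligibility is verified, so those criteria should be settled before dosing. The point rests on the GCP clause instead.
- **Timing.** A reader might take it as fact that sets are chosen with outcomes in hand. The protocol does not date the meeting, and it does require the Per-Protocol deviations to be defined beforehand. That requirement does not reach the GCP clause.
- **Loss of the event.** A reader might infer that a harmed subject vanishes. Section 8.1 requires adverse events to be recorded in the case report form whatever the analysis set. The risk is to the incidence table, not to the record.
- **Decisiveness.** The study is descriptive and has no hypothesis or safety threshold. The intervals in the table overlap heavily, so one exclusion does not settle any formal decision.
- **Efficacy.** A reader might infer that Per-Protocol exclusions could inflate an improvement rate. The protocol defines no responder rate; it analyses change from baseline. Section 9.3.4 also requires the FAS result alongside the Per-Protocol one.

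None of this removes the nesting. It is stated protocol text on the population for the primary objective, not a detail left open for a statistical analysis plan.

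**Conclusion.** The point holds in a limited form. Followed literally, section 9.2 lets a subject who received the vector leave the only population defined for the primary safety objective, through an undefined GCP exclusion or the lack of a safety assessment. On one assumed event among 12 subjects, the reported incidence would move from 8.3% to 0% and the upper 95% limit from 38.5% to 28.5%.

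These figures show what the rule permits. They do not predict any event or exclusion, and nothing in the protocol suggests an intention to exclude anyone. The conclusion assumes that the Safety Set is the population for section 9.3.3, which is implied but not stated. The concern about membership being decided with outcomes known is an inference from the open-label design. The reference to an unnamed primary efficacy endpoint is a separate and smaller wording error in an exploratory analysis.

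**What to change.** In section 9.2, define the Safety Set as every subject who received any amount of rAAV2/8-hCYP4V2. State that membership does not depend on the FAS, eligibility, GCP status, availability of a post-dose assessment or any decision of the data review meeting.

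In section 9.3.3, state that adverse events and all other safety measures are analysed on that set.

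Separately, reword the Per-Protocol definition so that it does not refer to a primary efficacy endpoint.

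The safety problem does not require dropping the Per-Protocol Set, listing its criteria in the protocol or redefining the FAS; those are matters of preference or for the statistical analysis plan. The cost is a few sentences, with no extra data, visits or patients.
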